### Qualitative Interview Procedures

Each member of the qualitative people experiencing homelessness sample was asked to complete 3 semistructured qualitative interviews. The first interview, conducted over the telephone and audio recorded, focused on questions concerning participants’ (1) prehousing homelessness experiences; (2) experience obtaining PSH; (3) health, social services, and social experiences prior to and after obtaining PSH; and (4) management of COVID-19–related safety and concerns. These interviews lasted approximately 30-60 minutes each. The second and third interviews were conducted 3 and 6 months after the baseline interviews and used photo elicitation interviewing (PEI), a method that uses photographs taken by participants to guide interviews [22]. This method enhances the depth of each interview and increases the capacity to identify potential topics of interest that were not part of the study’s original data collection plan. PEI is also an effective tool for building rapport, gaining access to participants’ lived experiences, and relieving the strain of direct, extended verbal questioning, which can be particularly taxing for participants with cognitive or mental disabilities [23-25]. All client PEI interviews were conducted over the phone and lasted approximately 45 minutes. Each interview was recorded and transcribed for analysis, and participants received a US $50 gift card incentive of their choice (Visa, Amazon, or Target) after each interview.

### PEI Methods

Participants were asked to use their study-issued cellphones to take photos that represent their daily lives and experiences in their housing placement for a 2-week period. There was no limit on the number of photos they could take, though they were asked to avoid taking any identifiable photos of any individuals to protect privacy. Participants were then asked to choose 5-10 of the photos that best captured their recent experiences and email or text them to the study coordinator, who then provided them to the interviewer. At the outset of each interview, interviewers asked participants to choose whichever photo they wanted to discuss first. For this photo and subsequent images, participants were asked first to describe each photo and then elaborate on how it reflects their recent experiences related to housing, health, service use, COVID-19 protection, safety, resources, relationships, personal growth, and daily functioning. Participants were also asked to come up with a title or theme that collectively described the photos they discussed, if there was anything they wanted to take a photo of but could or could not, and why, and any recommendations for improvements in services for others experiencing homelessness based on the photos. If any participant did not feel comfortable using the phone camera, they were offered the alternative of taking “mental snapshots,” in which they made a list of 5-10 things they wished to discuss and shared this list with their interviewer. For the second PEI at the 6-month follow-up, participants were asked to go through the same procedures. However, during this PEI, participants were asked to focus on how things changed for them across the different domains and compare their photos from the 2 PEIs.

### Focus Groups

Provider group interviews concentrated on learning provider perspectives on the difference between PB-PSH and SS-PSH, the strengths and weaknesses of each model in improving outcomes for people experiencing homelessness, and the impacts of the COVID-19 pandemic on PSH service delivery. Each focus group met for approximately 60 minutes and was conducted either in person or via Zoom, depending on the housing agency’s preference. As with the client interviews, staff focus groups were recorded and transcribed for analysis, and participants received a US $50 gift card incentive of their choice (Visa, Amazon, or Target).

### Quantitative Analysis

The statistical analysis will rely on bivariate and multivariate regression analysis to examine the relationship between PSH (SS-PSH vs PB-PSH) and quality of life and COVID-19–related health behaviors. For outcomes, we will use a pre-post design that treats Month 1 as the baseline and Month 6 as the endline and compares pre-post changes for SS-PSH and PB-PSH. For outcomes sensitive to monthly trajectory variation, we will use fixed-effects and random-effects models of monthly outcomes that test for interaction between the PSH model and months of exposure to each PSH type. These models will be informed by an analysis of baseline variation between SS-PSH and PB-PSH clients. We expect variations in the level of baseline morbidity. Thus, we will use both multivariate models that account for baseline differences and propensity score matching models that establish an area of common support for SS-PSH and PB-PSH comparisons. We will use calendar-month controls to account for historic changes in the ecology of health behavior, particularly in relation to rising and falling rates of COVID-19. We will also address the potential need for multilevel or mixed-effects models to account for potentially shared experiences by housing and service providers. Additional models will test for differences in housing outcomes by race, ethnicity, sex, and gender via interaction effects and stratified models. Further analysis will entail the use of a path modeling framework to understand the pathways leading from PSH types to outcomes of interest. Due to the decision to include “prefer not to answer” as an option for all questions, all analyses will account for the frequent use of this response option. In cases where “prefer not to answer” is a common or meaningful response option, such as regarding partisan political affiliation or experiences of trauma, we will include it as a response option. In cases where “prefer not to answer” appears to reflect a random nonresponse pattern, we will treat the value as missing, use multiple imputations to maintain sample size, and conduct robustness checks comparing the imputed and raw samples.

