**Methods:**

People experiencing homelessness who are placed in either PB-PSH or SS-PSH completed 6 monthly surveys after move-in using smartphones provided by the study team. A subsample of participants completed 3 qualitative interviews at baseline, 3 months, and 6 months that included photo elicitation interviewing. Two stakeholder advisory groups, including one featuring people with lived experience of homelessness, helped guide study decisions and interpretations of findings.

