### Design Overview

This study leveraged Los Angeles County’s ongoing efforts to provide PSH to people experiencing homelessness during the COVID-19 pandemic using a mixed methods, prospective longitudinal design. We recruited people moving into PSH and provided them with smartphones with paid data plans to stay connected with the study for a 6-month period. All study participants were recruited through organizations that provide housing, supportive services, or both. Although PB-PSH is clearly defined in the homelessness services system, SS-PSH could have been officially categorized as a PSH program or a rapid rehousing program. Although rapid rehousing programs are typically short-term housing programs with time-limited and tailored assistance programs, during the pandemic, Los Angeles County expanded the use of rapid rehousing programs coupled with supportive services to quickly provide access to housing. Thus, for this study, we considered anyone receiving rapid rehousing assistance to be SS-PSH if they also received support services, and examined whether those receiving rapid rehousing differ in terms of demographics, health status, or homelessness histories.

For the study’s quantitative arm, participants completed a baseline survey followed by 5 monthly follow-up surveys once in housing. For the qualitative arm, we recruited a purposive subsample of people experiencing homelessness from both PB-PSH and SS-PSH who participated in 3 semistructured interviews; the first was an in-depth interview when they initially moved into PSH, followed by 2 follow-up interviews conducted 3 and 6 months later. Focus groups with housing providers from the affiliated housing agencies were also conducted. Study protocols for each study component are described separately in more detail.

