### Recruitment of Study Participants

People experiencing homelessness were eligible to participate in the study if they were 18 years or older, had been approved for PSH, could be interviewed in English or Spanish, and were willing to provide informed consent. Enrollment included people experiencing homelessness who had been approved for PSH in Los Angeles County and had either been housed in the past 2 weeks or were expected to be placed in housing in 30 days. PSH placement is determined through a county-run coordinated entry system that identifies clients’ needs and matches them with available housing options. Because the system typically assigns individuals approved for PSH to specific nonprofit, community-based agencies that are ultimately charged with securing housing and supportive services, recruitment was conducted through 26 agencies. The study began recruitment in January 2021 amid a significant surge in the COVID-19 pandemic in Los Angeles County. Therefore, in-person recruitment was not a viable option and instead depended on the case managers at each program, who were already interacting with people experiencing homelessness as part of the housing placement process. The study team relied on these agencies to inform anyone approved for PSH (or rapid rehousing who would be receiving supportive services) about the study. Study staff members then coordinated a meeting with the eligible people experiencing homelessness interested in the study via phone or Zoom to complete the enrollment process. Although this process remained largely intact throughout the recruitment period, in-person recruitment occasionally occurred when COVID-19 rates were low and visitors were allowed at program sites.

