### Enrollment and Quantitative Data Collection Procedures

To enroll, an agency staff member initiated the referral process for people experiencing homelessness by contacting the research recruitment team via phone, email, or text. A research recruitment team member then followed up to schedule an appointment with the potential participant to complete a screening to ensure eligibility, review the consent form, and answer any questions related to the study protocols. Case managers then distributed study phones that had been shipped to the recruitment site. Participants received a Samsung A01 Core smartphone with an unlimited data and calling plan, which allowed them to provide electronic informed consent and complete a self-administered questionnaire sent via text message. Participants were enrolled in the study once they provided informed consent by completing a web-based form that assessed study comprehension and documented their electronic signature.

Initially, participants completed a 20-minute survey upon enrollment in the study to capture basic demographic and historical information about their housing and health. Baseline outcome measures were then administered in a follow-up survey approximately 1 day later to help reduce the burden involved in completing a lengthy questionnaire at the time of enrollment. Participants received a US $15 electronic gift card incentive for completing the baseline outcome measure survey. Participants who enrolled in the study prior to moving into a housing unit were asked to complete a second baseline outcome measures survey once they moved in and received another US $15 electronic gift card incentive. After moving into PSH and completing the demographic and baseline surveys, participants received 5 monthly follow-up surveys and received a US $15 electronic gift card incentive for each completed survey. Participants could also complete surveys over the phone if they preferred to speak with a surveyor rather than self-administer the survey. Electronic gift cards were sent to an email address provided by the participant. The survey links were all sent via text message. The study team, in consultation with the LEG, opted to allow “prefer not to answer” as a response option for all historical and monthly survey questions to reduce any frustration among those who were not sure how to answer and minimize the possibility that some questions could be triggering given high rates of past trauma.

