**Patients experiencing homelessness** **population characteristics: covariates measured at baseline only** **[18]**		
	Predisposing	Demographics (ie, age, gender, marital status, and veteran status); health beliefs (ie, knowledge of disease and health services attitudes); social structure (ie, race and ethnicity, education, employment, religion, trauma, and homelessness history); systems involvement history (eg, foster care, criminal justice, and trauma); housing preference
	Enabling	Income, insurance, benefits, case management, food insecurity, and social support
	Need	Chronic physical disease, serious mental illness, and substance use disorder; baseline measures for physical and mental health status as noted in outcomes
**Patient-centered outcomes: quality of life including physical, mental, social, and environment health, and measured monthly**		
	Life satisfaction	NIH^a^ Toolbox Item Bank v2.0 General Life Satisfaction (10 items, self-rated life satisfaction) [19]
	Physical health	PROMIS^b^ Global Health Scale Version 1.2 (PROMIS; 2 items, self-rated physical health and activities) [19]
	Mental health	PROMIS (2 items, self-rated mental health, frequency bothered by symptoms) [19]
	Social health	PROMIS (1 item, self-rated satisfaction with social activities and relationships) [19]
	Environmental health	Housing retention and Housing Environment Scale (4 items, residential satisfaction; 12 items, neighborhood quality and safety) [20]

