## Results

Study recruitment was supposed to occur over 6 months starting in January 2021 but was extended due to delays in recruitment. These delays included COVID-19 delays (eg, recruitment sites shut down due to outbreaks and study team members testing positive) and delays that may have been indirectly related to the COVID-19 pandemic, including high staff turnover or recruitment sites having competing priorities. Given these delays, data collection and analysis are expected to be completed in 2023. As depicted in the consort diagram (see Figure 2), at the end of recruitment in July 2022, a total of 641 people experiencing homelessness had been referred from 26 partnering recruitment sites, and 563 people experiencing homelessness had enrolled in the study and completed a baseline demographic survey. Of the 641 referrals, 37 were not eligible to participate due to not meeting the criteria, 20 declined to participate, and our recruitment team could not reach 21 to complete enrollment. Of the 563 participants in the study, 452 had recently moved into the housing when they enrolled, with 272 placed in PB-PSH and 180 placed in SS-PSH. Another 111 participants were approved but are still waiting for housing placement. To date, 49 participants have been lost at follow-up, with 21 opting out of the study, 22 who could not be reached, and 6 participants who died.

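### The Month 1 'baseline' is taken after move-in, so the pre-post contrast estimates change after move-in and removes any housing-type effect already present, most clearly for the Housing Environment Scale

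*Protocol article*

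**What the plan says.** For its outcomes the Quantitative Analysis section states: "we will use a pre-post design that treats Month 1 as the baseline and Month 6 as the endline". The changes are then compared between SS-PSH and PB-PSH. For outcomes that vary month by month it adds fixed-effects and random-effects models, in which the tested term is the interaction of PSH type with months of exposure. Multivariate adjustment for baseline differences and propensity score matching are also planned.

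The timing of the surveys is given elsewhere in the article:
- Abstract, Methods: participants "completed 6 monthly surveys after move-in using smartphones provided by the study team".
- Design Overview: "participants completed a baseline survey followed by 5 monthly follow-up surveys once in housing".
- Recruitment of Study Participants: enrolment took in people who "had either been housed in the past 2 weeks or were expected to be placed in housing in 30 days".
- Enrollment and Quantitative Data Collection Procedures: "Baseline outcome measures were then administered in a follow-up survey approximately 1 day later". People who enrolled before moving in were "asked to complete a second baseline outcome measures survey once they moved in".
- Results: of 563 enrolled, "452 had recently moved into the housing when they enrolled, with 272 placed in PB-PSH and 180 placed in SS-PSH". The other 111 were still waiting for placement.

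Table 1 lists environmental health among the patient-centered outcomes, measured by housing retention and the Housing Environment Scale ("4 items, residential satisfaction; 12 items, neighborhood quality and safety"). Setting and Conceptual Model hypothesises that PSH type affects quality of life, and counts housing and neighborhood characteristics as part of it.

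**The concern.** A pre-post comparison isolates an effect only if the first measurement precedes the exposure. Here both measurements are taken in housing. An advantage that appears on moving in and persists is in both values and cancels.

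For residential satisfaction and for neighborhood quality and safety, the first in-housing answer is about the unit and area the person has just been given. It is an outcome of placement, not a pre-value. If one type of housing is better from move-in and stays better, this contrast would show no difference, although the hypothesis is about exactly that difference. The Conclusions say that the study can influence future public health approaches, so it matters whether a null result means equal housing or equal drift after move-in.

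**Working it through.** **1. Is Month 1 after exposure?** A baseline plus 5 monthly follow-ups makes 6 waves, which matches the 6 monthly surveys after move-in in the Abstract. Month 1 is not defined, but it is most naturally the in-housing baseline wave. For people already housed at enrolment that wave falls at most about 14 + 1 = 15 days after move-in. People enrolled earlier repeat the outcome survey once housed. If Month 1 means the first follow-up instead, exposure is about a month longer. On neither reading does Month 1 precede housing.

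**2. Who could have a pre-housing value?** Read literally, Results has 452/563 = 80.3% housed at enrolment and 111/563 = 19.7% not yet housed. Only the latter could have a pre-move-in outcome survey, and the planned contrast does not use it. The Discussion words the 452 differently and leaves open whether some of them enrolled before moving in.

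**3. What the contrast estimates.** Let D be the true type effect at Month 6, f the share of it present at Month 1, and S a stable selection gap between the groups.
- Expected gap at Month 1: S + fD
- Expected gap at Month 6: S + D
- Difference in changes: (S + D) − (S + fD) = (1−f)D

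Differencing removes S, which is its merit, and fD, which is its cost.

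**4. Size.** The article gives no effect size, SD, correlation or alpha. Assumed for illustration: D = 0.30 SD, two-sided alpha 0.05, 272 vs 180, Month 1–Month 6 correlation ρ of 0.5 or 0.7, no attrition or clustering. The SD of a change is √(2(1−ρ)), which is 1 at ρ = 0.5. The standard error is then √(1/272 + 1/180) = 0.096 SD.

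| f | Expected change contrast (SD) | Power, ρ=0.5 | Power, ρ=0.7 |
|---|---|---|---|
| 0 | 0.300 | 87.7% | 98.1% |
| 0.25 | 0.225 | 64.9% | 85.6% |
| 0.5 | 0.150 | 34.5% | 52.2% |
| 0.75 | 0.075 | 11.9% | 17.0% |
| 1 | 0 | 2.5% (upper tail) | 2.5% (upper tail) |

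At ρ = 0.5, z falls from 0.30/0.096 = 3.1 at f = 0 to 0.15/0.096 = 1.6 at f = 0.5. A simulation with D = 0.30, f = 0.5, ρ = 0.6 and no selection gave a mean of 0.149 with the Month 1 baseline and 0.299 with a pre-housing baseline.

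**5. Do the other planned models restore the loss?**
- Person fixed effects: PSH type is constant within a person, so a constant level difference is absorbed. The interaction with months of exposure is a slope in housing.
- Month 1 outcome as covariate: the expectation is D(1−ρf). At f = ρ = 0.5 that is 0.30 × 0.75 = 0.225, so part of the early effect is still lost.
- Random effects: a PSH main effect would keep the level difference, mixed with residual selection. The article names the interaction as the test.

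**6. Health care use.** The look-back is 180 days. If Month 1 is the baseline wave, at most 15/180 = 8% of the window is in housing, so the Month 1 value is nearly a pre-value. If it is the first follow-up, taken as about 30 days later, the figure is 45/180 = 25%.

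**The case against.** The strongest reply is that placement was not randomized. Limitations says so and adds that case-manager referral may introduce selection, and the analysis section expects the groups to differ in baseline morbidity. The Month 1 gap is therefore selection plus any early effect, and differencing is a defensible way to remove stable selection. A Month 6 level contrast keeps whatever selection the covariates miss. Under the same kind of assumption, a stable unmeasured gap of −0.15 SD would pull a true 0.30 down to 0.15, the same loss as f = 0.5. This stands, and it is why the change contrast should be kept for outcomes that Month 1 can reasonably anchor. It does not rescue the environmental items: their Month 1 value is the rating of the assigned unit, so it cannot serve as a measure of prior selection.

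A second reply is that change with time in housing was the intended question, since the models test months of exposure and Limitations refers to time in housing as the original plan. If so, the contrast needs that label. The stated aim is comparative effectiveness of the two models, which is broader.

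Two stronger readings are tempting. A reader might infer that the study as a whole would report no difference whenever an effect is immediate. The documents do not support that: regression of outcomes on PSH type, propensity matching and random-effects models are also planned, and an analysis of baseline variation could show a Month 1 gap. A reader might also infer that pre-move-in surveys should replace Month 1 as the baseline wherever they exist. Read literally, Results says that none of the 452 housed participants has one. Using them for some people only would mix change scores that are not comparable, possibly unevenly by PSH type.

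**Conclusion.** The point holds in a limited form. The pre-post contrast is an in-housing change, and any type effect present at Month 1 is subtracted together with stable selection differences.

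- **Environmental health.** For the Housing Environment Scale outcomes this is a wrong choice of contrast: the Month 1 value is itself an outcome, and a difference that is immediate and lasting shows as zero.
- **Life satisfaction, physical, mental and social health.** The loss is (1−f)D with f unknown. After 0 to 15 days in housing f may be small, so this calls for correct labelling and a companion contrast rather than replacement.
- **Health care use.** The loss is small if Month 1 is the baseline wave.

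The figures above show the range under assumed D, ρ and f and do not predict this study's result. The documents do not support calling the Month 1 baseline invalid for every outcome.

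**What to change.** 1. For residential satisfaction and neighborhood quality and safety, make the PSH-type difference in level at Month 6 the main contrast, with Months 1 to 5 shown. Adjust or propensity-weight on pre-housing covariates only, not on the Month 1 outcome.
2. For life satisfaction, physical, mental and social health, keep the Month 1 to Month 6 change, call it change after move-in, and report the adjusted Month 6 level contrast beside it.
3. Define Month 1 as either the in-housing baseline wave or the first follow-up.
4. Use pre-move-in outcome surveys only in a sensitivity analysis restricted to participants who have one.
5. Reconcile the Abstract and Results, which describe the 452 as already housed at enrolment, with the Discussion, which describes them as recruited participants moving into housing. State how many housed participants have a pre-move-in survey.

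The cost is analysis-plan wording and one more model per outcome, with no new data. The drawback is that the level contrast is more exposed to unmeasured selection, which is why both contrasts should be reported for the non-environmental quality-of-life outcomes.
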